#### Outcomes

2.4.2

The primary outcome will be the assessment of discrepancies in suicide risk estimates across study groups (between-subjects) and the evaluation of the stability of individual risk appraisal tendencies over time (within-subject), in order to identify specific patterns and factors that may influence variability and inter-rater agreement in risk estimation across different clinical scenarios.

The secondary outcome is the assessment of discrepancies in suicide risk estimates between the C-SSRS and No-C-SSRS conditions, in order to determine whether the use of a standardized suicide risk assessment instrument will lead to greater homogeneity in risk ratings across the study groups. To allow comparison of discrepancies between the two subgroups, suicide risk assessment will be expressed as categorical variables for participants assigned to the C-SSRS condition (low, moderate, high) and as ordinal scores for participants in the No-C-SSRS condition (from 1 to 9). Cut points were defined *a priori* to represent three clinically interpretable categories of risk intensity, corresponding to low (scores 1-3), intermediate (4–6), and high (7–9) perceived risk. This mirrors the three-level structure imposed by the C-SSRS while preserving the ordinal distribution of the original ratings (**Table 1**).

**Table 1 T1:** Conversion of the suicide risk estimates between the C-SSRS and No-C-SSRS conditions.

C-SSRS condition risk categories	No-C-SSRS condition risk scores
Low risk	1-2–3 scores
Moderate risk	4-5–6 scores
High risk	7-8–9 scores

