To account for expected attrition at follow-up, the planned sample size was increased to at least 500 participants. This choice was informed by evidence from a recent study by Kolochowski et al. (20), which used the same set of vignettes adopted in the present protocol and reported a follow-up completion rate of 55.9 percent. Assuming a conservative attrition rate of approximately 40 to 45 percent, an initial sample of 500 participants would result in a final sample of approximately 275 to 300 individuals, which remains adequate for the planned longitudinal and within-subject analyses. The online administration format and broad inclusion criteria further support the feasibility of achieving this sample size.

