To quantify inter-rater agreement across raters for each vignette, Krippendorff’s alpha will be used as the primary agreement index, as it is appropriate for multi-rater settings with potentially unbalanced data. Weighted kappa coefficients will be computed only in supplementary pairwise comparisons to facilitate interpretability relative to commonly reported agreement metrics. Within-person analyses will evaluate the stability of participants’ overall level and pattern of risk estimates across time using different vignette sets drawn from the same risk-calibrated pool. These analyses do not represent test–retest reliability of identical stimuli but rather the temporal consistency of risk perception. Because different vignettes of the same risk category will be administered at baseline and follow-up, within-person analyses will be conducted on participant-level summary indices (e.g., central tendency of ratings and distribution of risk categories across vignettes at each time point) rather than on vignette-level paired comparisons. For the No-C-SSRS condition, paired non-parametric tests, such as the Wilcoxon signed-rank test, and correlation analyses will be used. For the C-SSRS condition, indices of temporal consistency will be computed to evaluate the stability of participants’ overall tendency to classify scenarios into risk categories across time, rather than agreement on identical stimuli.

The mixed-effects framework described above will also be used to examine interaction effects. Pre-specified interaction terms will examine whether differences in risk estimation vary as a function of demographic and professional variables (e.g., age, gender, years of clinical experience, prior suicide-specific training) across study group and experimental condition. In addition, to control for inflation of Type I error due to multiple comparisons, p-values from secondary analyses will be adjusted using the false discovery rate approach.

Missing data will be handled under a missing-at-random assumption using maximum likelihood estimation within mixed-effects models, which allows inclusion of all available observations without listwise deletion. Attrition between baseline and follow-up will be examined descriptively, and sensitivity analyses will compare participants who completed follow-up with those who did not. Predictors of attrition will be explored to assess potential systematic differences between completers and non-completers.

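### The maximum-likelihood missing-data rule covers only the mixed models, so the individual stability analyses are unadjusted completer analyses on about 275 to 300 of 500 participants

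*Protocol article*

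**What the plan says.** Section 2.4.2 (Outcomes) makes within-subject stability part of the primary outcome: "the evaluation of the stability of individual risk appraisal tendencies over time (within-subject". HP4 (within-subject variability by clinical exposure) and the within-subject part of HP5 depend on it.

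Section 2.5.2 (Planned statistical analysis) gives one missing-data method, under a missing-at-random assumption: "maximum likelihood estimation within mixed-effects models, which allows inclusion of all available observations without listwise deletion". The same section takes individual stability out of those models, because "within-person analyses will be conducted on participant-level summary indices". In the No-C-SSRS condition, "paired non-parametric tests, such as the Wilcoxon signed-rank test, and correlation analyses will be used". In the other arm, "For the C-SSRS condition, indices of temporal consistency will be computed to evaluate the stability"; the index is not named.

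On dropout, section 2.5.1 (Power analysis) writes "Assuming a conservative attrition rate of approximately 40 to 45 percent" and counts 275 to 300 people for the longitudinal and within-subject work. Section 2.5.2 adds a description of attrition, a search for its predictors, and that "sensitivity analyses will compare participants who completed follow-up with those who did not". Section 2.6 makes follow-up depend on a voluntarily given email address, and the Discussion accepts that this may cause self-selection.

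**The concern.** A signed-rank test or a baseline-to-follow-up correlation cannot use a person with one assessment. The same must hold for any index comparing one person's two time points. These analyses therefore drop non-returners, and the likelihood rule does not reach them.

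The rule's missing-at-random assumption allows return to depend on observed baseline data. Likelihood estimation in a correctly specified mixed model is valid under that assumption. Complete-pair statistics are in general not; they need the stricter condition that return is unrelated to the ratings. So the individual stability results can be biased even if the plan's own assumption is true. If return depends on ratings differently in different groups or conditions, the comparisons for HP4 and HP5 are affected as well, and randomisation does not protect a comparison made among returners only.

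**Working it through.** **Inputs from the protocol.** Initial sample 500; attrition 40 to 45 percent; completion in the study that supplied the vignettes 55.9 percent; two conditions; ten groups.

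**The plan's own figure.** 500 × (1 − 0.40) = 300 and 500 × (1 − 0.45) = 275, which reproduces the stated 275 to 300. At 55.9 percent completion, 500 × 0.559 = 279.5. People without a pair: 500 − 300 = 200 to 500 − 275 = 225. With equal allocation, about 138 to 150 pairs per condition. With equal group sizes as well (an assumption), about 14 to 15 per group-by-condition cell.

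**What the mixed models cover.** Section 2.5.2 specifies random intercepts for participants and, where appropriate, for vignettes, with fixed effects for group, condition, time and their interactions. The time terms estimate average change, and how it differs by group and condition, from all available ratings. A single random intercept gives each person one level common to both occasions. As specified, the model therefore does not estimate how well a person's baseline level predicts the follow-up level, nor whether within-person variability differs with exposure. Those questions rest on the complete-pair indices.

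**Do complete pairs fail under missing at random?** An illustration with assumed inputs: standardised baseline and follow-up summaries, true mean change 0, true correlation r of 0.3, 0.5 or 0.7, completion 55.9 percent, and log-odds of return rising by s per SD of baseline level.

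| True r | s | Complete pairs: change (SD) | Complete pairs: r | Likelihood, everyone: change | Likelihood, everyone: r |
|---|---|---|---|---|---|
| 0.3 | 0.5 | −0.139 | 0.291 | 0.004 | 0.299 |
| 0.3 | 1.0 | −0.253 | 0.275 | 0.002 | 0.299 |
| 0.5 | 0.5 | −0.103 | 0.487 | 0.001 | 0.498 |
| 0.5 | 1.0 | −0.181 | 0.465 | 0.002 | 0.498 |
| 0.7 | 0.5 | −0.063 | 0.690 | 0.000 | 0.700 |
| 0.7 | 1.0 | −0.109 | 0.667 | 0.002 | 0.699 |

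With s = 0 the complete pairs are unbiased. The false change is regression to the mean: returners were selected for high baseline values. If low raters returned more often, its sign would reverse. Weighting returners by the inverse of their true return probability also gave a change of about 0 and the true r. The effective sample was about 95 percent of returners at s = 0.5 and 80 percent at s = 1.0.

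**Scale.** At r = 0.5 the SD of the change is √(2 × (1 − 0.5)) = 1. With 140 pairs its standard error is 1/√140 = 0.085, so a false change of 0.10 to 0.18 is about 1.2 to 2.1 standard errors. For a correlation of 0.60, the standard error (1 − 0.36)/√(n − 1) is about 0.05 with 138 to 150 pairs and about 0.17 with 15. A bias of 0.01 to 0.03 is smaller than either.

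**The case against.** The strongest reply is that nothing is misstated or hidden. The missing-data sentence limits itself to mixed models, the power section counts 275 to 300 for the within-subject work, and the Discussion names self-selection. This stands: a reader might infer that the protocol promises no listwise deletion for the paired tests, and it does not. But disclosure and completer comparisons can only reveal selection; they change no estimate. Nor is this only detail left to an analysis plan, since the article itself fixes both the rule and the methods that the rule cannot reach.

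A reader might also infer that the within-subject part has no likelihood cover at all. That goes too far, because average change over time is covered by the mixed models.

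A reader might infer that stability will be overstated, because engaged people return. The documents do not establish this. If return depends on an unmeasured carefulness trait that also lowers rating noise, returners' correlations were 0.62 to 0.67 against a true 0.60 under one set of assumptions. With return depending on baseline level they were too low. Nor does unequal retention between groups alone bias stability within a group; return must also relate to ratings or stability there.

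On the remedy, the objection is partly right. In the carefulness scenario, weights built from the level and spread of baseline ratings left the correlation almost unchanged in three of four settings and overshot in the fourth (0.668 became 0.555). Weighting cannot remove selection on something not measured.

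Finally, a change in Krippendorff's alpha from baseline to follow-up would mix time with a change of raters, but the protocol plans no such contrast, so this is no fault of the plan.

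**Conclusion.** The point holds in limited form. The individual stability analyses behind the within-subject part of the primary outcome, HP4 and HP5 are completer analyses on about 275 to 300 of 500 self-selected returners, without adjustment. For the unnamed C-SSRS index this is an inference, though any index comparing two occasions in one person needs both. The loss of 200 to 225 people follows from the plan's own figures. The bias does not: it is zero if return is unrelated to the ratings, can take either sign otherwise, and may be modest. The illustrated values (0.06 to 0.25 SD in mean change, 0.01 to 0.03 in correlation) rest on assumed correlations and return slopes. The change is worth making before data are seen, because the direction of any error could not be judged reliably afterwards.

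**What to change.** In section 2.5.2, label the signed-rank tests, correlations and temporal-consistency indices as completer analyses, and pre-specify an adjusted version of each, reported beside the unweighted one. Choose one of two routes:

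- **Weighting.** Weight returners by the inverse probability of follow-up, estimated from baseline data held on everyone: condition, study group, age, sex, experience, prior training, and the level and spread of the six baseline ratings.
- **Modelling.** Estimate stability within the mixed model, using correlated participant effects for baseline and follow-up, so that the stated likelihood rule applies.

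State that either route corrects only for selection on measured data. The cost is some wording, one extra model and wider intervals; no new data are needed. With about 14 to 15 returners per group-by-condition cell, the weighting model should be kept simple and its effective sample size reported.

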### Data access and management

2.6

Data will be managed and stored within the Department of Pathophysiology and Transplantation at the University of Milan and will be accessed exclusively by the study investigators and will not be shared with other operational units. All collected data, including personal data, will be the exclusive property of the University of Milan, and no external parties will have access to them. The questionnaire will be administered through a dedicated link redirecting participants to the Qualtrics platform. Responses will be collected directly through Qualtrics and subsequently organized into a study-specific database. Participation in the baseline questionnaire will be completely anonymous. At the end of the baseline survey, participants will be invited, on a fully voluntary basis, to provide an email address exclusively for the purpose of receiving the follow-up questionnaire link. Providing an email address will not be mandatory for participation in the study, and individuals may complete the baseline survey without leaving any contact information. Contact information will be used solely for follow-up communication and will not be included in the analytical dataset. Following data extraction, study variables and suicide risk estimates results will be entered into an electronic database for statistical analysis. In accordance with applicable data protection regulations (General Data Protection Regulation, EU Regulation No. 2016/679), all collected data will be stored confidentially for a period of ten years within the Department of Pathophysiology and Transplantation at the University of Milan.

### Ethics and regulatory approval

2.7

The study protocol of the CARE project was reviewed and approved by the ethics committee of the University of Milan (Ref: 91/25), and all subjects will provide electronic informed consent in accordance with the Declaration of Helsinki.

## Discussion

3

This study protocol outlines an innovative research project designed to examine both between-person and within-person variability in suicide risk estimates across several groups, including mental health professionals, other health professionals, medical and psychology students, and individuals from the general population. The study aims to produce evidence that can support enhancements in the training of healthcare professionals and the development of more consistent and reliable risk assessment strategies. Rather than attempting to improve statistical prediction of suicidal behavior, the CARE study focuses on the variability of human judgment in suicide-related situations, an issue that remains highly relevant even in clinical models that prioritize individualized formulation over categorical risk stratification. Furthermore, the study evaluates the effect of a brief, scalable training on a standardized instrument, the C-SSRS, reflecting real-world conditions in which such tools are frequently introduced without extensive training. Therefore, a transversal objective of this study is to determine whether the use of a standardized instrument, the C-SSRS, may reduce subjectivity in judgment and promote greater uniformity in suicide risk estimates across clinical and non-clinical participants. Indeed, understanding how non-professionals estimate suicide risk is important because individuals frequently encounter situations involving psychological distress in family, social, or workplace contexts, where interpretation of warning signs may influence help-seeking or referral behaviors. Additionally, by presenting different yet comparable vignettes at follow-up, the study examines whether individuals display stable risk attribution patterns across contexts, an approach that more closely reflects real-world clinical decision-making where identical cases are never reencountered.

Suicide risk assessment is challenging and often inaccurate, even among experienced clinicians, particularly when it relies on subjective risk categorization (21). Furthermore, studies have shown that the use of risk scales or psychosocial assessment protocols has not significantly improved the reliability of suicide prediction (28–30). This issue can be attributed, at least in part, to insufficient training in suicide risk assessment among healthcare professionals, who often exhibit an ambivalent attitude toward suicide, which substantially affects prevention efforts and clinical decision-making (31). Additionally, many psychologists tend to avoid treating patients at high suicide risk (32), and most healthcare professionals lack suicide specific knowledge, often without having received any training in suicide prevention or assessment (33). This limitation undermines their ability to recognize warning signs and effectively identify individuals at greatest risk (34, 35). For example, in a study of 670 healthcare professionals, among those who had experienced the suicide loss of a patient, 44% reported that they had not received adequate professional training on suicide-related knowledge (36). Conversely, completing suicidology training increases confidence and improves the management of suicide risk, even among early career psychiatrists and trainees (37). In the general population, although knowledge about suicide can be lifesaving across all contexts, it is often extremely limited and consistently shaped by misconceptions, prejudices, misinformation, and stigma across different cultures (38–40).

Given these considerations, the expected findings of the CARE project have the potential to yield meaningful insights regarding the impact of brief suicidology training and the use of a standardized tool for suicide risk assessment, the C-SSRS, among healthcare professionals and the general population. Furthermore, identifying the study groups that exhibit greater variability in suicide risk estimates, along with the academic and professional factors associated with this variability, may inform the development of targeted psychoeducational interventions aimed at improving the accuracy and consistency of suicide risk estimates. The results of this project may also guide refinements in professional training for psychiatrists, psychologists, nurses, and other healthcare providers by promoting the integration of standardized assessment practices and structured decision-making. However, recruitment through online dissemination constitutes a convenience sampling strategy and may limit representativeness. Participants may differ from non-participants in terms of interest in suicidology, motivation, or prior exposure to suicide-related content. Although efforts will be made to recruit across diverse healthcare settings and institutions, findings should be interpreted with caution regarding generalizability to all clinicians or to the broader general population. The primary objective of the study is comparative, focusing on relative differences in risk appraisal patterns across groups rather than population-level estimates. In addition, because participation in the follow-up assessment requires participants to voluntarily provide contact information (e-mail) after completing an otherwise fully anonymous baseline survey, a self-selection bias may be introduced, whereby individuals who agree to be recontacted could differ systematically from those who choose to remain anonymous. Ultimately, comparing healthcare professionals and the general population may offer valuable insights for planning awareness campaigns and preventive interventions that extend beyond clinical settings, including educational, community-based, and public health environments. A deeper understanding of how laypeople interpret warning signs and estimate suicide risk, indeed, may support the development of more effective communication strategies, thereby improving early recognition of risk and facilitating timely referral to appropriate services.

Overall, this project will represent one of the largest and most comprehensive initiatives aimed at comparing suicide risk assessment among mental health professionals, other healthcare professionals, and the general population. It will also provide insight into the effects of using standardized tools such as the C-SSRS on inter-rater and intra-rater variability, ultimately generating knowledge that can meaningfully contribute to strengthening suicide prevention efforts.
